### Provisions for post-trial care {30}

All participants will be offered routine medical and surgical post-trial care commensurate with their condition at the discretion of the treating surgeon. There will be no compensation offered to participants either for their involvement in the study. This is outlined in the participant information and consent form.

### Outcomes {12}

#### Primary outcome

The primary outcome will be the side-to-side difference in anterior tibial translation as measured on the GNRB arthrometer at 2 years post-operatively, between groups. Maximum anteroposterior tibial translation at 134 N will be recorded on both the operative and non-operative knees pre-operatively and post-operatively at 3, 12 and 24 months. The goals of ACL reconstruction are to restore sagittal and rotatory stability to the knee and to prevent secondary injuries such as meniscal tears, and progression to osteoarthritis [35]. Common means of assessing this is by comparison of pre- and post-operative subjective Lachman manoeuvre and anterior drawer; however, these are often imprecise and subjective [36]. Consequently, devices to accurately measure anterior tibial translation have been developed, most popularly the KT-1000 ™ manual arthrometer (MEDmetric®, San Diego, USA) [37]. However, this device has been criticised for poor inter- and intra-observer reliability, and as such, newer computerised models such as the GNRB (Genourob, Laval, France) have been developed, with improved reliability [38]. Studies have utilised these arthrometers to compare between anterior cruciate ligament surgical techniques, such as graft types [39, 40], assessing post-operative outcomes [41], as well as analysing residual joint laxity after ligament reconstruction [42]. This outcome has been selected due to its ability to assess whether the addition of suture tape in ACLR results in knee stability that is more similar to the contralateral uninjured knee than standard ACLR technique. Anterior tibial translation and knee laxity may vary from individual to individual, and for this reason, side-to-side difference has been chosen as the primary outcome, allowing the contralateral knee to be a within-participant baseline measure, reducing the variability in outcome owing to between participant differences.

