### Sample size {14}

All statistical methods and power analysis were developed through consultation with an independent statistician. Power analysis was performed with G*power 3.1 Software. To achieve a minimum 80% statistical power with an alpha value of 0.05, power analysis based on a hypothesised mean residual side-to-side difference of 2 mm of anteroposterior tibial translation yielded a sample size of *n*=48 (24 per group) utilising an expected independent *t*-test [47–50]. Although previously published KT-1000 data was utilised for power analysis, it has been shown that the GNRB exhibits similar absolute measures in side-to-side anterior tibial translation to KT-1000 utilised by experienced observers, whilst having reduced scatter around the mean [38]. This would mean that utilising KT-1000 published data to establish a power analysis would be a conservative method, and likely over-estimate the required sample size to detect significant differences.

Secondary power analysis based on 2-year IKDC total scores yielded a total sample size of 48 (*n*=24 in each group) to detect significant differences with 80% power and an alpha value of 0.05 with an anticipated independent sample two-tailed *t*-test. This is based on a previous retrospective study of suture-tape ACL reconstruction which reported a mean change from baseline IKDC of 56 ± 17 in SA-augmented ACLR, compared with 38 ± 25 in conventional ACLR [29, 51]. Secondly, previous studies evaluating the IKDC [51] which reported that a change score of 12.8 points would be sufficient to detect differences between those who have and have not had improved knee outcomes. Power analysis yielded a sample size of 48. Dropout rates are expected to be 30% based on institutional experience, owing to loss to follow-up and contralateral ACL rupture and graft failure, and as such 66 patients will be recruited. This is expected to take approximately 1–2 years of recruitment based on historical institutional caseloads.

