## Statistical methods

### Statistical methods for primary and secondary outcomes {20a}

Side-to-side difference in anterior tibial translation (the primary outcome), overall ACL-RSI, EQ5D-5L, Marx activity scales, IKDC and KOOS-QOL will be calculated as means, with measures of dispersion reported as standard deviation. Differences between groups will be reported as mean differences, with dispersion reported with confidence intervals. Data normality will be assessed with the Shapiro-Wilk test for continuous parametric assessment. Between-group comparisons, such as the primary outcome of mean difference in GNRB anteroposterior laxity at 2 years, will be assessed with independent samples *t*-tests. If data is found to be non-parametric in distribution, the Wilcoxon rank sum test will be utilised. Comparison of two dichotomous variables, such as return to sport rates and complication rates, will be performed with Fischer’s exact test. Repeated measures such as GNRB measures and mean PROMs will be assessed using mixed effects linear analysis. All tests are two-sided. A *p* value of <0.05 will be considered the cut-off for statistical significance.

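### The primary t-test fixes the slope on the contralateral knee at 1; adding the pre-operative contralateral translation as a covariate is a low-cost gain in precision that may be small or nil

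*Protocol article*

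**What the plan says.** Under Outcomes {12}, Primary outcome, the protocol article states: "The primary outcome will be the side-to-side difference in anterior tibial translation as measured on the GNRB arthrometer at 2 years post-operatively". It gives two reasons for the side-to-side form. One is clinical: whether the reconstructed knee behaves more like the uninjured one. The other is statistical: "allowing the contralateral knee to be a within-participant baseline measure, reducing the variability in outcome owing to between participant differences". The same section says that translation at 134 N "will be recorded on both the operative and non-operative knees pre-operatively and post-operatively at 3, 12 and 24 months".

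Statistical methods {20a} fixes the comparison: "Between-group comparisons, such as the primary outcome of mean difference in GNRB anteroposterior laxity at 2 years, will be assessed with independent samples" *t*-tests, with a rank sum test if the data are not normal. No covariate is named. The section adds "Repeated measures such as GNRB measures and mean PROMs will be assessed using mixed effects linear analysis", again with no contralateral term. Sample size {14} uses the same unadjusted t-test for 2 mm and gives 24 per group. It states no SD for the side-to-side difference, no SD for either knee and no correlation between knees.

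**The concern.** A t-test on operated minus contralateral is a regression on the contralateral knee with the slope set to 1. If the true slope differs from 1, part of the contralateral knee's variation stays in the outcome as noise that a fitted slope would remove. A reconstructed and a native knee need not track each other one for one, and each reading carries its own measurement error.

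Precision is at stake, not validity. The plan aims for 80% power at 24 per arm. Its own 30% dropout applied to 66 leaves 66 × 0.7 = 46.2, about 23 per arm, where the same assumptions give 78%. The contralateral knee is already measured before randomisation, so any available precision costs no data.

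**Working it through.** **Inputs from the article.** Difference 2 mm, 24 per group (Sample size {14}); "To achieve a minimum 80% statistical power with an alpha value of 0.05"; "All tests are two-sided" (Statistical methods {20a}).

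**Assumptions.** O and C are the operated and contralateral translations at 24 months, with SDs sO and sC. Let k = sC/sO and r = corr(O, C). The ranges used are r 0.3 to 0.8 and k 0.7 to 1.2. The contralateral knee's correlation between the pre-operative and 24-month visits is taken as 0.8.

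**1. The plan's own figure.** No SD is stated, so the 24 per group can only be back-solved. A two-sided t-test with 24 per arm and 80% power needs a standardised effect of 0.826, so SD = 2/0.826 = 2.42 mm. SDs from about 2.37 to 2.42 mm all round up to 24. I use 2.42.

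**2. When subtraction helps.** Var(O − C) = sO² + sC² − 2·r·sO·sC. This is below sO² only if r > sC/(2·sO) = k/2. The threshold is 0.35 at k = 0.7, 0.425 at 0.85, 0.50 at 1 and 0.60 at 1.2. With k = 1, Var(O − C)/Var(O) = 2(1 − r): 1.4 at r = 0.3, 1.0 at 0.5 and 0.6 at 0.7.

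**3. Same-visit contralateral value as covariate.** Residual variance is sO²(1 − r²). Var(O − C) minus this equals (sC − r·sO)², which is never negative and is zero only when r = k, that is, when the true slope is 1. Relative to the plain difference, the variance is (1 − r²)/(1 + k² − 2rk). Power is for 2 mm at 24 per arm, from the noncentral t with SD 2.42 × √(ratio):

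| r | k = 1: variance cut | power | k = 0.7: variance cut | power |
|---|---|---|---|---|
| 0.3 | 35% | 93.5% | 15% | 86% |
| 0.5 | 25% | 90% | 5% | 82% |
| 0.7 | 15% | 86% | 0% | 80% |
| 0.8 | 10% | 84% | 3% | 81% |

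At k = 1.2 the cuts are larger (47%, 40% and 33% at r = 0.3, 0.5 and 0.7).

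**4. Pre-operative contralateral value P as covariate (k = 1).** The proportion of variance removed is corr(O − C, P)² = (corr(O, P) − 0.8)²/(2(1 − r)). The result depends on how O relates to P, so two cases are shown: (a) corr(O, P) = r; (b) corr(O, P) = 0.8r.

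| r | (a) cut | power | (b) cut | power |
|---|---|---|---|---|
| 0.3 | 0.25/1.4 = 18% | 87% | 0.32 × 0.7 = 22% | 89% |
| 0.5 | 0.09/1.0 = 9% | 84% | 0.32 × 0.5 = 16% | 86% |
| 0.7 | 0.01/0.6 = 2% | 81% | 0.32 × 0.3 = 10% | 84% |
| 0.8 | 0/0.4 = 0% | 80% | 0.32 × 0.2 = 6% | 83% |

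In case (b) the expression simplifies to 0.32(1 − r).

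**5. Worst case.** The formulas above ignore the lost degree of freedom and chance covariate imbalance. A simulation of the same-visit model at 24 per arm (20,000 trials), at the tie point k = 0.7, r = 0.7, gave estimator variance 0.493 adjusted against 0.484 unadjusted, and power 79.1% against 80.3%. At k = 1 the simulated power was 93%, 89% and 85% at r = 0.3, 0.5 and 0.7, close to the table.

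**The case against.** The strongest reply is that nothing here is an error. The t-test on the difference is unbiased, it matches the sample-size test, and the side-to-side form has a clinical reason that does not depend on variance. That stands. It does not make the point one for the analysis plan alone, because the article itself fixes the primary comparison as an unadjusted test.

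A reader might infer that subtraction adds noise whenever the knees correlate below 0.5, and hence that the article's rationale is false. The documents do not support this. The 0.5 threshold needs equal SDs in the two knees, which are not given. The article speaks of variability due to differences between participants, and subtraction does remove the part shared by both knees. What is not shown is that total variance falls.

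A reader might also take 93.5% as the power on offer. That figure needs the same-visit covariate, equal SDs and r = 0.3. With k = 0.7 and r = 0.7 the gain is nil.

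Finally, the same-visit value is measured after randomisation. Criteria for discontinuing {11b} allows the arthrometer analysis to change after a contralateral rupture, which would compromise that covariate (and the side-to-side difference itself). The pre-operative value precedes randomisation but gains less.

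The SD of 2.42 mm is back-solved. Sample size {14} argues that the GNRB scatters less than the KT-1000 data used, so the plan may have some margin. That weakens the urgency, not the direction.

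**Conclusion.** The planned comparison is valid and unbiased but possibly inefficient, and its variance rationale is unsupported by any figure in the article. In large samples, adjusting for the contralateral value is never worse than the plain difference. The size of the gain is uncertain. With the pre-operative covariate it is roughly 0% to 22% of the variance (power about 80% to 89% at 24 per arm, against 80%), assuming SD 2.42 mm, equal knee SDs, visit-to-visit correlation 0.8 and r 0.3 to 0.8. With the same-visit covariate it is 10% to 35% if the SDs are equal (84% to 93.5%), but only 0% to 15% at an SD ratio of 0.7 (80% to 86%). This is a worthwhile improvement, not the correction of a mistake.

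**What to change.** Keep the 24-month side-to-side difference as the primary outcome. Pre-specify that the arm difference is estimated from a linear model of it on arm plus the pre-operative contralateral translation at 134 N, and report the unadjusted difference as supportive. The effect stays in millimetres with the same meaning.

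A model using the 24-month contralateral value can be a sensitivity analysis; its treatment estimate is identical to that from regressing the operated knee on arm and the contralateral knee. That identity does not hold for the pre-operative covariate.

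The cost is one line of analysis text, one degree of freedom and, at worst, about one point of power. No additional measurement is needed.

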#### Secondary outcomes

Secondary outcomes are fourfold and will include (i) PROMs, (ii) return to sport rates, (iii) complications and (iv) examination findings.i)PROMs will be recorded preoperatively and post-operatively at 6 weeks, 3 months, 12 months and 24 months. PROMs collected will include the following:EQ5D-5L: The EuroQol EQ-5D-5L is a validated, generic, self-reported outcome measure covering five health domains that are used to facilitate the calculation of quality-adjusted life years (QALYs) in health economic evaluations. The original EQ-5D questionnaire contained three response options within each of five health domains (mobility, self-care, usual activities, pain/discomfort and anxiety/depression) [33]. More recently, the EQ-5D-5 L has been developed to overcome problems with ceiling effects and to improve sensitivity [43]. The 5 L version consists of the same five domains as the original but with five response options.The International Knee Documentation Committee (IKDC) score: The IKDC is a knee-specific patient outcome questionnaire often used after ACL reconstruction [31]. It is a subjective tool that provides an overall patient score (0–100), often interpreted as a measure of function, where higher scores represent a greater function. It aims to address three categories: symptoms, activity and overall function, and has shown adequate test-retest reliability and good construct validity in patients with issues at the knee [44].Knee injury and Osteoarthritis Outcome Score Quality of Life sub-scale (KOOS-QOL): This subscale is a 4-item questionnaire designed to evaluate the knee-specific quality of life, has been utilised among ACL surgical trials [30] and has been established to have validity, responsiveness and reliability in patients undergoing ACLR [45].ACL return to sport index (ACL-RSI): Psychological readiness to return to sport will be evaluated with the ACL-RSI. It is a 12-point questionnaire validated to evaluate a patient’s confidence and readiness to return to sport [34] and exhibits high internal validity and structural consistency [46]. Given the theoretical increased stability offered by suture tape augmentation, particularly in the early rehabilitative period, it follows that patients treated with this may experience improved perception of knee function and subsequent confidence in rehabilitation and sporting activity across the early postoperative period.Self-reported pain: We will record postoperative pain levels and long-term knee pain scores utilising 10-point visual analogue scale pain scores (VAS) where 0 is no pain and 10 is the worst pain imaginable.ii)Complications:We will record complications and adverse events including wound complications, infection rates, return to surgery, e.g. meniscal tears, graft failure, contralateral knee ACL rupture, residual effusion, rates of symptomatic arthrofibrosis of the knee and second look arthroscopy findings and the rates of sterile effusion. These will be recorded upon review of each patient’s medical record at 2 years.iii)Return to sport and activity:Return to sport and activity will be assessed via a self-reported questionnaire delivered concomitantly with PROMs preoperatively and post-operatively at 6 weeks, 3 months, 12 months and 24 months. Return to activity will be evaluated through the Marx activity scale, a four-item activity rating scale which has been shown to have excellent retest reliability in patients with knee injuries [32]. Participants will be asked to record on a scale of 0–4 how often they are able to perform each of running, cutting, deceleration and pivoting in their most active state across the preceding 12 months. A maximum score is 16 points. Participants will also be asked about their dichotomous return to sport status, their expectations regarding timing of return to sport, return to preinjury level of sport and the time postoperatively to return to sporting activity. These questions, along with the full set of pre-operative and post-operative PROMS, are included in Additional file 1.iv)Examination findingsExamination findings will be taken preoperatively at examination under anaesthesia and post-operatively at 6 weeks, 3 months and 12 months. Examination findings including the range of motion (ROM), the presence of knee effusion, Lachmans, pivot shift and anterior drawer testing will be recorded. All assessments will be undertaken by lead surgeons S.T, L.B.

### Participant timeline {13}

Participants will be recruited from the orthopaedic outpatient clinic at our institution. Participants will be eligible for assessment if they are referred to either of the associated investigators’ clinic (L.B or S.T) and are consented for ACLR. Eligibility for trial participation based on inclusion and exclusion criteria will then be assessed. Patients who are eligible will be offered a discussion about the study and the opportunity to ask questions in line with best-practice informed consent. Data will be collected pre-operatively and post-operatively at four time points (6 weeks, 3 months, 1 year and 2 years) and will include arthrometric measure of anterior tibial translation on the GNRB arthrometer and PROM-based data, as well as return to sport data, complication rates and examination findings (Fig. 1). Participants will then be asked to complete an online questionnaire about their injury, preoperative return to sport expectations and PROMs. Following this, they will be referred for routine preoperative rehabilitation and undergo preoperative GNRB assessment with a member of the research team. Demographic data will be extracted from their medical record with the participant’s consent at this time. Initial examination findings will be recorded at examination under anaesthesia preceding arthroscopy. Final evaluation of eligibility criteria will occur during arthroscopy. Those patients who have consented for involvement in the study and are deemed eligible during surgery will be randomised using the REDCap platform and allocated to one of the trial arms (ACLR or ST-ACLR) and blinded to the allocation (Fig. 2).

**Fig. 1 Fig1:**
[figure not shown]
SPIRIT figure summarising outcomes and assessment schedule

**Fig. 2 Fig2:**
[figure not shown]
Trial flow pathway

Postoperatively, all GNRB measurements will be taken at the same standard time points to routine surgical follow-up by a member of the research team, or a member of the physiotherapy unit familiar with GNRB protocols. All PROMs and return to sport data will be recorded via online surveys directly into the REDCAP database. Follow-up surveys will be conducted via automated email service at the corresponding time point. All subsequent examinations will be conducted by lead surgeons S.T and L.B with data entered directly into a study data collection report form (paper version), and then manually entered into the REDCAP database. There will be only one time point (2 years) at which patients will be required to attend follow-up (for GNRB testing) without the need for a standard clinical follow-up as per standard practice; otherwise, patients will be within the hospital for their standard clinical follow-up at the time of testing.

### Sample size {14}

All statistical methods and power analysis were developed through consultation with an independent statistician. Power analysis was performed with G*power 3.1 Software. To achieve a minimum 80% statistical power with an alpha value of 0.05, power analysis based on a hypothesised mean residual side-to-side difference of 2 mm of anteroposterior tibial translation yielded a sample size of *n*=48 (24 per group) utilising an expected independent *t*-test [47–50]. Although previously published KT-1000 data was utilised for power analysis, it has been shown that the GNRB exhibits similar absolute measures in side-to-side anterior tibial translation to KT-1000 utilised by experienced observers, whilst having reduced scatter around the mean [38]. This would mean that utilising KT-1000 published data to establish a power analysis would be a conservative method, and likely over-estimate the required sample size to detect significant differences.

Secondary power analysis based on 2-year IKDC total scores yielded a total sample size of 48 (*n*=24 in each group) to detect significant differences with 80% power and an alpha value of 0.05 with an anticipated independent sample two-tailed *t*-test. This is based on a previous retrospective study of suture-tape ACL reconstruction which reported a mean change from baseline IKDC of 56 ± 17 in SA-augmented ACLR, compared with 38 ± 25 in conventional ACLR [29, 51]. Secondly, previous studies evaluating the IKDC [51] which reported that a change score of 12.8 points would be sufficient to detect differences between those who have and have not had improved knee outcomes. Power analysis yielded a sample size of 48. Dropout rates are expected to be 30% based on institutional experience, owing to loss to follow-up and contralateral ACL rupture and graft failure, and as such 66 patients will be recruited. This is expected to take approximately 1–2 years of recruitment based on historical institutional caseloads.

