Recently, the use of suture tape (a modified suture composed of non-absorbable, braided polyethylene/polyester suture) acting as a ‘seatbelt’ for in situ autograft has been proposed [15–17]. It differs from historical graft augments in its ‘addition’ to autograft rather than replacement of it, and its successful use in ligamentous reconstruction and repair in other joints is encouraging [18–20]. Notably, the use of suture tape may improve initial graft stability and protect the graft prior to ligamentisation. Significantly, it has been studied to exhibit improved biomechanical stability relative to non-augmented grafts [21–23]. Additionally, animal studies have reported equivalent functional, arthroscopic and histological findings between augmented and unaugmented knees [24–27]. Importantly, rates of persistent synovitis, rates of graft incorporation and incidence of adverse histological findings are not reported to differ between suture-tape augmented grafts and control grafts among animal models [24, 27]. A recent human model report of 36 ACL reconstructions with suture tape augmentation recorded no persistent joint effusion or evidence of synovitis [28]. However, prospective clinical data is lacking. A 2019 retrospective comparative study of 60 knees exhibited reduced postoperative pain, as well as improved change from baseline PROMs at 1 year after all-inside ACLR with suture-tape augmentation [29]. However, this study is limited both in its retrospective design and its lack of objective assessment of knee stability. In contrast to this study, Parkes et al. have reported on 36 suture tape-augmented reconstructions, finding no significant differences in rates of return to sport, mean IKDC scores or post-operative examination findings compared with a 2:1 matched cohort [28]. Whilst these studies offer promise regarding possible benefits of suture tape augmentation, they lack a control group and complete clinical assessment to the standard 2-year mark post-operatively. Significantly, the influence of graft augmentation upon residual anterior knee laxity after reconstruction of the ACL has not been reported across the literature. This study aims to address these deficits.

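### The IKDC power statement lists a 12.8-point change score as a second basis for 48 patients, but 48 follows only from the 18-point difference in change from baseline

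*Protocol article*

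**What the plan says.** Sample size {14} of the Protocol article gives a second power calculation beside the one for the primary GNRB outcome. It opens: "Secondary power analysis based on 2-year IKDC total scores yielded a total sample size of 48", that is 24 per group, "to detect significant differences with 80% power and an alpha value of 0.05 with an anticipated independent sample two-tailed" t-test.

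Two supports follow. The first is a retrospective study of suture-tape reconstruction that "reported a mean change from baseline IKDC of 56 ± 17 in SA-augmented ACLR, compared with 38 ± 25 in conventional ACLR". The second, introduced as a further point, is earlier work on the IKDC reporting that "a change score of 12.8 points would be sufficient to detect differences between those who have and have not had improved knee outcomes". The next sentence repeats that the analysis gave 48, and the text moves on to dropout. It does not say which of the two figures the 48 belongs to.

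Two other places bear on this. Background and rationale {6a} describes the same retrospective study as showing "improved change from baseline PROMs at 1 year after all-inside ACLR with suture-tape augmentation". Statistical methods {20a} summarises IKDC as means and SDs, compares groups by independent t-test, assigns repeated PROMs to a mixed linear model, and states: "All tests are two-sided".

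**The concern.** A reader meets two differences, 18 and 12.8 points, and a single sample size placed after both. The natural inference is that 48 patients serve either one. Since 12.8 is much smaller than 18, that cannot be so with the same variability.

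The labels also do not match. The calculation is named for 2-year total scores, but its inputs are changes from baseline. The background section indicates that they were observed at 1 year.

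IKDC is the only secondary outcome for which the article states a power, and better PROMs are a secondary hypothesis in its Discussion. If the IKDC comparison is not significant, someone relying on this paragraph could take the trial to have had 80% power for 12.8 points on the 2-year score. The paragraph's own figures do not show that.

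**Working it through.** **Inputs**, all from Sample size {14} unless noted:
- mean change 56 (SD 17) with tape and 38 (SD 25) without
- cited change score 12.8
- two-sided α 0.05 (also Statistical methods {20a}), power 80%, independent t-test
- 24 evaluable per group, 1:1 allocation (Sequence generation {16a})

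**Step 1: pooled SD.** √[(17² + 25²)/2] = √[(289 + 625)/2] = √457 = 21.38.

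**Step 2: reproduce the stated 48.** Difference 56 − 38 = 18, so d = 18/21.38 = 0.842. At n = 24 per group the noncentrality is 18/(21.38 × √(2/24)) = 2.92 on 46 degrees of freedom, which gives power 81.5%. At 23 per group it is 79.7%, so 24 is the smallest n that reaches 80%. The plan's figure is reproduced. A simulation with unequal SDs of 17 and 25 gives 81.3% (Welch) and 81.5% (pooled t), so the unequal variances do not matter here.

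**Step 3: smallest difference with 80% power at 24 per group.** 17.7 points.

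**Step 4: the same calculation at 12.8 points.** d = 12.8/21.38 = 0.599; noncentrality 12.8/(21.38 × √(2/24)) = 2.07.

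| SD of change | Power at 24 per group | n per group for 80% |
|---|---|---|
| 17 (tape arm) | 72% | 29 |
| 21.38 (pooled) | 53% | 45 |
| 25 (standard arm) | 41% | 61 |

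The Welch simulation gives 52.6% at 12.8 points. If all 66 recruited patients were evaluable (33 per group), power at the pooled SD would be 67%. For 24 per group to give 80% at 12.8 points, the SD would have to be about 15.5, below both quoted SDs.

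**Step 5: how far this carries to 24-month scores.** The article gives neither an SD for the 24-month score nor a correlation r between baseline and follow-up. Suppose, as an assumption, that the SD is the same at both times. A change-score SD of 21.38 then implies a score SD of 21.38/√[2(1 − r)], and a baseline-adjusted residual SD of 21.38 × √[(1 + r)/2]. Power for 12.8 points at 24 per group is then:

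| r | 24-month score, unadjusted | 24-month score, adjusted for baseline |
|---|---|---|
| 0 | 82% | 82% |
| 0.3 | 67% | 71% |
| 0.5 | 53% | 65% |
| 0.6 | 44% | 62% |

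So 53% describes an unadjusted comparison of change scores. For the 24-month score the power depends on r, and adjustment for baseline helps at every r above zero.

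**The case against.** The strongest reply is that nothing has been miscalculated. The 48 is right for the retrospective figures it is said to rest on. The 12.8-point sentence describes a cut-off that separates patients who improved from those who did not. It can be read as context showing that 18 points exceeds a known threshold, with the repeated 48 as a recap before the dropout step.

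Much of this stands. A reader might infer that the protocol calls 12.8 points a meaningful difference between arms and claims 80% power for it. The text does not say so: it describes a patient-level threshold. That leaves the sentence with no role in a two-sample calculation, yet it is listed as a second support and followed by the same total, so the wording still needs correcting.

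A reader might also infer that the trial's power for 12.8 points on 24-month IKDC is 53%. The documents do not support that either, because the figure rests on change-score SDs and no adjustment. Step 5 shows values on both sides of it.

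The 1-year timing is likewise an inference. The sample size section gives no time point for the 56 and 38, and the link comes from the background section's account of the same reference.

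Finally, IKDC is secondary, and the GNRB calculation arrives at 48 by itself. Between-group differences are to be reported with confidence intervals, so a reader could set the interval beside 12.8. That limits the harm but does not make the power statement correct.

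**Conclusion.** The point holds in a limited form. The 48 evaluable patients are justified for a difference of about 18 IKDC points in change from baseline (power 81.5%; 17.7 points for exactly 80%). They are not justified for 12.8 points. On the quoted SDs, an unadjusted t-test on change scores has about 53% power for 12.8 points, with a range of 41% to 72%, and would need 45 per arm, 90 in total.

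The stated power also belongs to a different quantity from the one named: change from baseline, apparently at 1 year, rather than the 2-year total score.

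These figures assume that the retrospective SDs apply to this trial. This is a fault in how the basis of the figure is presented, not an error in the figure.

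**What to change.** In Sample size {14}:
- State that 48 evaluable patients give about 80% power for an 18-point difference in IKDC change from baseline, based on retrospective change-score data (pooled SD 21.4). Give the time point of those data, and remove the 2-year total-score label from this calculation.
- Remove 12.8 points as a basis for 48. Alternatively, keep it as a patient-level threshold and report that an unadjusted comparison of change scores has about 53% power for a between-arm difference of that size (41% to 72% over the quoted SDs). Add that power for 24-month scores depends on a baseline correlation the protocol does not give.

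In Statistical methods {20a}, specify that 24-month IKDC is compared with adjustment for baseline IKDC, which is already collected before surgery, and that the adjusted difference is reported with its confidence interval.

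The cost is a few sentences and a less favourable stated power for a secondary outcome. The number recruited, the assessments and the primary GNRB calculation do not change.
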